### Evaluated outcomes

#### Primary outcome

Duration of exclusive breastfeeding: the child who is exclusively breastfed, without the introduction of water, tea, liquids, milk supplementation, or food introduction, as recommended by the World Health Organization [35].

### Secondary outcomes

Nipple-areolar lesions: lesion(s) in the nipple-areolar region(s) with or without disruption of the skin barrier.Nipple or breast pain: verbal report of pain, describing its characteristics, associated with breastfeeding.Breast complications: occurrence of engorgement or mastitis.Exclusive breastfeeding in the first, fourth, and sixth months of life: exclusive breastfeeding in this period.Postpartum depression scores: measured by the Edinburgh Scale, indicated for tracking signs indicative of puerperal depression, which should be applied after the persistence of symptoms of puerperal blues, that is, with continuity of symptoms after 1 month and consistent with the birth.Hospitalizations and occurrence of illnesses in childhood: based on the mothers’ report to the telephone contact.Weaning: interruption of breastfeeding, considered early, when it occurs before 4 months of the child’s life.Care complexity of the dyads: classification into minimal, intermediate, semi-intensive, and intensive care, based on the care required by postpartum woman and newborn.Performance of the postpartum women and newborn during breastfeeding: based on the validated scale (LACTH) application.

### Statistical methods

#### Sample size

The sample size will be calculated by a statistician with no clinical involvement in the research and obtained after carrying out the pilot study.

Previously, a pilot study will be conducted with 60 participants being recruited, 20 participants from each center, 10 allocated in the intervention group, and 10 in the control group for each center. To achieve a high confidence level for a pilot study, a minimum sample of 50 research subjects is recommended [36]. A significance level of 5% and a statistical power of 95% will be considered, and the sample calculation will be performed after analyzing the pilot study, as well as follow-up losses will be considered, using the OpenEpi version 3.01 program.

### Statistical analysis

Data will be entered into a Google Forms® form, saved as Microsoft Excel® spreadsheets, and imported into the statistical program Social Package for the Social Sciences (SPSS) version 23.0 and analyzed in this same program and OpenEpi version 3.01. The data analysis will be of the type by the finalization of the protocol, denominated explanatory.

In characterizing the allocation groups in the research, measures of absolute and relative frequencies will be used for the categorical variables. Numerical variables will be summarized using measures of central tendency (mean or median) and dispersion (standard deviation, minimum, and maximum).

To verify the relationship between the exposure variable and the outcomes, Pearson’s *χ*^2^ and Fisher’s exact tests will be used for categorical variables and Student’s *T* test or Mann–Whitney, for numeric variables, considering a significance level of 5%, relative risks and their 95% confidence intervals. From the initial analysis, analyses of subgroups and adjusted analyses will be used.

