### Study design

This is a multicenter, randomized, superiority, parallel, and open clinical trial guided by the international recommendations of the Consolidated Standards of Reporting Trials [14].

The randomized clinical trial is considered the gold standard for evaluating health interventions, establishing a causal relationship, and evaluating the effectiveness of the intervention [15].

This is a superiority study, because it will determine whether the investigational intervention is superior to the comparator; parallel study, as each group of participants will be exposed to only one intervention studied (intervention or control); random, as participants will be allocated between groups, and each individual has the same probability of being selected for one group or another [16, 17]; and open, as there will be no masking of the intervention (participants and researchers) [18–21], because it would be impossible to blind this intervention for women and nurses. However, data analysis will be carried out by researchers not directly involved in data collection.

This clinical trial protocol was designed following the Standard Protocol Items: Recommendations for Interventional Trials (SPIRIT) [22] as evidenced in the checklist (see Additional File 1).

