### Inclusion and exclusion criteria for participants

Will be included in the study, primiparous, aged over 18 years; who were pregnant with a single fetus, with live birth, gestational age of 37 to 42 weeks, birth weight greater than 2500 g, regardless of the type of delivery; who are hemodynamically stable, conscious, and oriented and admitted to the rooming-in wards, of the participating centers, at the time of allocation for the study.

Postpartum women and newborns with contraindications for breastfeeding (HIV positive; HTLV 1 and 2 positive or neoplastic treatment with chemotherapy) will not be included; infants with malformations that prevent or make breastfeeding difficult or with changes in breastfeeding mechanics (lingual frenulum); puerperal women whose infants were immediately separated after clamping the umbilical cord at birth due to maternal-neonatal complications, in which one or both were hospitalized in critical units; postpartum women transferred from other institutions or who have already been discharged (rehospitalization), postpartum women using illicit drugs, postpartum women with intellectual or sensory disabilities with a medical diagnosis. These criteria contemplate the feasibility of the intervention and the necessary follow-up to the clinical trial.

Women who are not followed up in the first month, after three unsuccessful attempts at contact and at least one contact with a family member at different times, will also be excluded if malformations or abnormalities in the mechanics of breastfeeding or changes in the mother–child bond are detected at the time of allocation.

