### Experimental group

In the intervention group, counseling will be carried out by a team of nurses qualified for breastfeeding management and counseling.

Women will be encouraged to answer the following open questions: How are you breastfeeding? Moreover, if she has doubts or concerns, they will be explored with: Tell me about it… Next, the following guiding question will be used: How are you feeling breastfeeding? Furthermore, in the end, you will be asked: What led you to breastfeed? The validated protocol for counseling on breastfeeding during hospitalization in rooming-in wards will be used for all responses.

Postpartum women allocated to this group will be approached using counseling, as described above. The researcher will collect the history of breastfeeding with the counseling approach and observe the breastfeeding. During breastfeeding, the LATCH [24] scale items will be observed—latching on, swallowing, type of nipple, comfort, and positioning. Afterward, the researcher will interview the puerperal woman and fill in sociodemographic, clinical, and obstetric data.

At the end of the first counseling session, the researcher will fill in the items of the scale adapted from the observation and evaluation form for rooming-in wards—Fantinelli’s scale [25], which measures the care complexity of the dyad.

Counseling will be offered twice a day until hospital discharge in the morning and afternoon, and the start and end times of the intervention will be recorded to determine the duration.

At the end of the intervention, the women will be invited to watch a videoscribe with the theme “Breastfeeding is better,” produced by the study group, in which the advantages of breastfeeding for the mother and newborn are discussed and guidance is given to seek help in case of breast complications. The video has three distinct versions, with the voices of the researchers of each center and a version in Brazilian Sign Language. The version adapted to the participant’s location will be used. The Brazilian Sign Language version was created for inclusion and health education purposes for these women but will not be used in this study.

The intervention (implementing individualized counseling on the duration of exclusive breastfeeding) will not require alteration to usual care pathways, including use of any medication for postpartum woman or neonates and these will continue for both trial arms.

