### Control group

The control group will receive standard institutional care, that is, the assistance offered by a professional, from the institution itself, without intervention by the researchers.

In these cases, the researcher responsible for data collection will conduct the interview and non-participant observation of at least one feeding without applying any intervention. The same instruments used in evaluating the intervention group will be applied. At the end of the interview, participants will also be invited to watch the videoscribe produced for the study.

Telephone contacts will be made, as well as in the intervention group, in the first and second weeks of life, with 1, 4, and 6 months of the child’s life to collect the outcomes.

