### Recruitment and data collection procedures

The researcher, daily, will go to the nurses responsible for the ward and locate the census of hospitalized puerperal women and identify the primiparous women who delivered at term and the bed in which they are hospitalized. The following information will be checked in the medical records: HIV and HTLV 1 and 2 serological test results; information on neoplastic diseases currently being treated with chemotherapy; neonatal malformations; diagnosis of neonatal ankyloglossia; description of separation at birth (hospitalization in critical units—women or newborn); readmission due to maternal or neonatal complications; illicit drug users; postpartum women with a medical diagnosis of intellectual difficulty or sensory deficit. If it has any of the present criteria, it will not be included in the list for randomization. If there are no criteria for non-inclusion, randomization will be performed. The gestational age and birth weight of neonates will also be checked.

Once the criteria are met, the researcher will go to the ward, explain the study’s objectives to the selected postpartum women and read the Informed Consent Form (ICF). When deciding positively to participate, the postpartum woman must sign the ICF in two copies, receiving a copy and another that the researchers will keep. The researcher will contact the randomization center, and eligible postpartum women will be randomized to the control or intervention group as directed by the center.

In the control group, the interview, evaluation of the breasts, and at least one feeding will be performed using the abovementioned instruments. At the end (zero time), the researcher will reinforce the telephone contacts and offer the videoscribe visualization. Unfilled information can be extracted from the medical records, and the care complexity scale will be filled in.

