In the intervention group, the postpartum woman will be approached with the strategy of counseling, breast evaluation, and at least one breastfeeding and interview according to a validated protocol. Ultimately, the researcher will reinforce the subsequent contacts, which will succeed in the allocation, interspersed in the morning and afternoon, depending on time zero, until hospital discharge. In the follow-up at the hospital, an approach with a counseling strategy will be carried out, identifying doubts and potential needs. In the end, the videoscribe will be offered and reinforced about subsequent telephone contacts for follow-up and their importance.

To characterize the sampling, the researcher will complete a daily list of eligible postpartum women, included or not included, and reasons for non-inclusion.

If the researcher detects abnormalities in the mechanics of breastfeeding or changes in the mother–child bond, the care team members will be notified, and the participant must be excluded.

Follow-up interviews will be done through phone calls. The researcher will make three telephone contact attempts at different times of the day: between 12:30 pm and 1:30 pm, from 4:00 pm to 5:00 pm, or at another preferred time indicated by the participant. If the attempt is unsuccessful, the researcher will try to contact the number provided by the family member. If accepted, the researcher will apply the questionnaire, thank them, and inform a new contact within a week. Contact will be made by the researcher who collected the data with the postpartum women included to maintain the link with the postpartum women and reduce sample losses.

In the second week, the same procedures will be carried out, but at the end, the researcher will signal a new contact in 2 weeks; in the first month, he will inform that he will return in 3 months, and on the fourth month, he will inform that the next call will be in 2 months. At the end of the protocol, the researcher will close the research and thank the participant.

Postpartum women who are not followed up in the first 15 days, after three unsuccessful contact attempts and at least one contact with a family member at different times, will be excluded.

All data will be completed in Google Forms® electronic forms on tablets purchased for this purpose. Only researchers will have access to the electronic database, collection instruments, and consent forms.

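### The only stated analysis of this superiority trial is restricted to completers, and women are excluded after randomisation, so the comparison loses the protection of randomisation

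*Protocol article*

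**What the plan says.** Under Study design the Protocol article states: "This is a multicenter, randomized, superiority, parallel, and open clinical trial". The analysis population is given under Statistical analysis, and the same sentence appears under Criteria for discontinuing the intervention: "The data analysis will be of the type by the finalization of the protocol, denominated explanatory". The article names no analysis of all randomised women. The subgroup and adjusted analyses it mentions do not change who is analysed.

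Allocation takes place on the ward after consent: "eligible postpartum women will be randomized to the control or intervention group as directed by the center" (Recruitment and data collection procedures). Three rules can remove women after that point:

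- Inclusion and exclusion criteria for participants: "Women who are not followed up in the first month, after three unsuccessful attempts at contact", and at least one contact with a family member, are excluded.
- Recruitment and data collection procedures: "Postpartum women who are not followed up in the first 15 days, after three unsuccessful contact attempts", with the same family contact, are excluded.
- The same section, where abnormal feeding mechanics or changes in the mother–child bond are found: "the care team members will be notified, and the participant must be excluded". The eligibility section ties this exclusion to the time of allocation.

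Contact before discharge differs by arm. Under Experimental group: "Counseling will be offered twice a day until hospital discharge in the morning and afternoon". Under Control group, the researcher does an interview and "non-participant observation of at least one feeding without applying any intervention".

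**The concern.** Completing the protocol and answering the telephone both happen after randomisation, and both may depend on how feeding is going and on the arm. Selecting women on such events can create a difference that is not there or hide one that is. Randomisation no longer guards against this, although the article relies on it for a causal conclusion about effectiveness against standard care.

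Three features of the plan sharpen the point.

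- The trial is open, and the researcher who saw the woman on the ward also makes the follow-up calls, expressly to preserve the relationship and limit losses. That relationship is built on repeated visits in one arm and on as little as one observed feeding in the other.
- Exclusion on detected mechanics or bonding problems depends on how often someone looks, and that differs by arm.
- The primary outcome is duration of exclusive breastfeeding (EBF). A woman who reports formula in the second week and cannot be reached at four months has an observed end of EBF. A completers analysis drops her.

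**Working it through.** **1. Is there a figure to reproduce?** No. The article gives no main-trial sample size, effect size or loss rate. Under Sample size these are left until after the pilot. What follows illustrates the consequence and does not estimate it.

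**2. Informative loss in one arm, no true effect.** Inputs:

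- p = 0.458 in both arms. The Discussion gives 45.8% as the Brazilian prevalence of EBF up to six months of age; using it as the six-month rate is an assumption.
- L = proportion lost (assumed 10% or 20% in each arm).
- r = EBF rate among the lost divided by p (assumed 0.5 or 0 in one arm; loss is random in the other, whose completers stay at 45.8%).

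Completers' rate = (p − L·p·r)/(1 − L).

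| L | r | Calculation | Completers | False difference |
|---|---|---|---|---|
| 0.1 | 0.5 | (0.458 − 0.0229)/0.9 | 48.3% | 2.5 points |
| 0.1 | 0 | 0.458/0.9 | 50.9% | 5.1 points |
| 0.2 | 0.5 | (0.458 − 0.0458)/0.8 | 51.5% | 5.7 points (RR 1.13) |
| 0.2 | 0 | 0.458/0.8 | 57.3% | 11.5 points (RR 1.25) |

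The sign depends on which arm has the informative loss. In the intervention arm it mimics benefit, and in the control arm it mimics harm.

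For scale, the Introduction cites RR 0.91 for weaning before the sixth month. Applied, as an assumption, to the 54.2% not on EBF, it is a true effect of 0.542 × 0.09 = 4.9 points.

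**3. Other loss patterns, including one without bias.** Let e and f be the losses among women on and not on EBF. Completers' rate = p(1 − e)/[p(1 − e) + (1 − p)(1 − f)]. There is again no true effect. The last column is the rejection probability of a two-sided 5% test of two proportions at 100, 200 and 400 randomised per arm (assumed sizes).

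| Control e/f | Intervention e/f | Control | Intervention | Rejection |
|---|---|---|---|---|
| 10%/20% | 10%/20% | 48.7% | 48.7% | 5%, 5%, 5% |
| 10%/10% | 10%/20% | 45.8% | 48.7% | 6.7%, 8.5%, 12.1% |
| 10%/10% | 10%/30% | 45.8% | 52.1% | 12.8%, 21.0%, 37.0% |
| 5%/15% | 5%/35% | 48.6% | 55.3% | 13.9%, 23.1%, 41.0% |

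In the first row each arm's rate is 2.9 points too high, but the arms do not differ. Where the pattern differs by arm, the false-positive rate rises with sample size.

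**4. Would censoring at last contact be enough?** Take the last row of step 2 with 100 women per arm, and suppose the 20 lost are lost before any later call. In the intervention arm 80 remain at risk and 45.8 are still on EBF. The Kaplan–Meier estimate is 45.8/80 = 57.3%, the same as for completers. In controls it is 36.64/80 = 45.8%. Counting lost women as having stopped gives:

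- both arms: 45.8% vs 36.6%, a false difference of 9.2 points;
- intervention arm only: 45.8% vs 45.8%, no difference;
- control arm only: 57.3% vs 36.6%, 20.6 points.

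No single assumption about the lost women is safe, so the range has to be shown.

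**The case against.** **The wording is translated.** Restriction to completers is an interpretation. It is the natural one, it fits the exclusion of unreached women, and the sentence stands in two sections. Because the article states this choice outright, it is not a detail left to an unseen analysis plan. The eligibility sentence on non-contact also runs two rules together. It is read here as two separate exclusions, because the recruitment section states them separately.

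**The sizes rest on chosen assumptions.** This stands. No loss rate is given, and nothing in the article shows that women who stop EBF are the ones who fail to answer. The illustration uses EBF at six months, a secondary outcome, whereas the primary outcome is duration. The 4.9-point yardstick transfers a weaning RR to EBF.

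**The plan takes steps against loss.** In both arms there are three call attempts, preferred times, a family contact and a familiar caller. Closer contact in the intervention arm could reduce loss there and leave the control losses as the more informative ones. This also stands, and it is why no direction can be claimed.

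**A stronger reading is tempting.** A reader might infer that the groups are no longer randomised at all, or that the analysis will favour counselling. The documents support neither. Women are still randomised, and what is lost is the protection randomisation gives to the comparison. With equal loss patterns the bias between arms in the example is nil.

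**Conclusion.** The point holds and should be corrected before the main trial is analysed. The article fixes a completers analysis as the only stated analysis of a superiority question. It also removes randomised women under two non-contact windows that contradict each other, and under a third exclusion whose timing is inconsistent between sections. Size and direction are unknown. They run from no bias between arms, if loss patterns are identical, to a false difference of about 2.5 to 11.5 points in either direction with no true effect. That range assumes 10% to 20% loss, informative in one arm only, and 45.8% on EBF at six months. Separately from any bias, EBF endings already observed in women lost later are thrown away.

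**What to change.** 1. Under Statistical analysis and Criteria for discontinuing the intervention, make the primary analysis all randomised women in the arm allocated. Keep the completers analysis as secondary.
2. Use every observed EBF status. Analyse duration with a time-to-event method that handles censoring and stopping observed only between calls, and add it to Statistical analysis. The tests now listed there (χ², Fisher, t, Mann–Whitney, relative risks) do not handle censored durations.
3. Add a sensitivity analysis for outcome-dependent loss. For example, count lost women as having stopped EBF after their last confirmed contact, in both arms and in each arm separately.
4. Reconcile the two non-contact windows, do not let either remove women from the analysis, and keep trying these women at the later scheduled calls.
5. Reconcile the two sections on when the mechanics/bond exclusion applies. Keep in the analysis any woman in whom it is detected after randomisation.

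Cost: a changed primary analysis method, some extra analysis and a few more calls. Because the sample size is not yet set, it should be calculated for this analysis; whether the number of women changes cannot be said now. The article already provides for documented protocol amendments.

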### Study location

The study will be carried out in the rooming-in wards of the hospitals: Clinics of the Federal University of Triangle Mineiro (HC-UFTM), in Uberaba (MG); Inacia Pinto dos Santos (HIPS), in Feira de Santana (BA) and at the Maternity School of the Federal University of Rio de Janeiro, in Rio de Janeiro (RJ).

In context, the Clinics of the Federal University of Triangle Mineiro (HC-UFTM) recorded 1259 deliveries in 2020. Reference for the resolution of high-risk pregnancies, infectious diseases in the pregnancy-puerperal cycle, for patients assisted in pathological prenatal care in municipalities in the Southern Triangle of Minas Gerais, and for pregnancies at usual risk located in the region of the institution and in all cities in the Southern Triangle of Minas Gerais that do not have a hospital. It is a public hospital with 100% of its services linked to the Unified Health System (SUS). It has 12 rooming-in beds and does not have the title of Baby-Friendly Hospital.

The Hospital Inacia Pinto dos Santos (HIPS) is characterized by being the first hospital in Bahia to receive the title of Baby-Friendly Hospital and being a reference in caring for women and newborns at normal risk. A public teaching hospital with three rooming-in units recorded 7501 deliveries in 2022 and has an installed capacity of 95 beds.

At the Maternity School of the Federal University of Rio de Janeiro, in 2020, 1607 births were recorded. Also characterized by public assistance and as a teaching hospital, its AC has nine wards totaling 45 active beds. Pregnant women of normal risk and those who need treatment for intercurrent illnesses or those related to pregnancy are assisted. The institution received the title of Baby-Friendly Hospital in December 2020.

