### Randomization, concealment of allocation, and masking

The sample will be probabilistic and calculated after conducting a pilot test with 60 postpartum women (20 in each center). A significance level of 5% and a statistical power of 95% will be considered. The postpartum women will be recruited by the research team, duly qualified for this action, and allocated through randomization by blocks composed of eight participants in two groups: intervention and control.

The randomization lists of each research center will be organized by a central of randomization, which will manage the allocation groups. This list will be prepared using the Randon® program. The researchers will contact the members of the randomization center to consult the order of inclusion of postpartum women in the research and their allocation group. This center will carry out allocation concealment, which will not be directly involved in the study data collection. There will be no blinding of participants and researchers involved in the collection.

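### Women are randomised from a separate list at each centre, but the named group comparisons do not account for centre; the effect is mild conservatism, and the remedy is a sentence

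*Protocol article*

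**What the plan says.** On allocation, the section on randomization, concealment and masking says: "The randomization lists of each research center will be organized by a central of randomization, which will manage the allocation groups". Women are "allocated through randomization by blocks composed of eight participants in two groups: intervention and control". The Sample size section shows the same within-centre balance in the pilot: "20 participants from each center, 10 allocated in the intervention group, and 10 in the control group for each center".

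On analysis, the Statistical analysis section says that Pearson's chi-square and Fisher's "exact tests will be used for categorical variables", and that Student's t or Mann-Whitney will be used "for numeric variables, considering a significance level of 5%, relative risks and their 95% confidence intervals". Centre is not named as a stratum, a covariate or a subgroup factor. The section closes with: "From the initial analysis, analyses of subgroups and adjusted analyses will be used".

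On the centres, the Study location section describes three different hospitals. The one in Uberaba is a referral hospital for high-risk pregnancies (1259 deliveries in 2020) and "does not have the title of Baby-Friendly Hospital". The one in Feira de Santana serves normal-risk women (7501 deliveries in 2022) and was the first in its state to hold that title. The one in Rio de Janeiro (1607 births in 2020) received it in December 2020. The control arm receives whatever each institution normally provides.

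**The concern.** Separate blocked lists force the arms to be balanced within each centre. That removes between-centre variation from the arm difference. A pooled chi-square or t test still counts that variation as noise, so it uses a standard error that is too large whenever centre predicts the outcome. The trial would pay for balance by centre and then not collect the benefit in precision.

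The protocol itself gives grounds to expect centre to matter: Baby-Friendly status, risk profile and the local standard of care all differ, and all plausibly bear on exclusive breastfeeding.

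The closing sentence raises a second, smaller issue. It ties adjusted and subgroup analyses to an initial analysis without saying whether that means order in time or selection by result.

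**Working it through.** The article states no sample size, effect size or centre-specific rate, because the sample size is deferred until after the pilot. There is therefore no figure of the plan to reproduce. The consequence of ignoring centre can still be sized.

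**Inputs from the article:** one list per centre; blocks of eight; alpha 5%; power 95%; a national exclusive breastfeeding prevalence of 45.8% (Discussion), rounded to 46% as the average rate.

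**Assumptions:** two-sided test; 1:1 allocation in the main trial; three equal-sized centres; the centre rates shown. With 1:1 blocks of eight, an incomplete last block can leave an imbalance of at most four women per centre, which is ignored here.

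**Formulas.** Let k be the mean within-centre p(1−p) divided by the pooled p(1−p). The pooled test uses variance V; the true variance of the arm difference is kV. Then:

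- interval width relative to a centre-stratified interval = 1/√k
- true type I error = 2 × [1 − Φ(1.96/√k)]
- power = Φ(1.960 + 1.645 − 1.96/√k), where the stratified test has 95%

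**Worked case, 30/46/62%.** Within-centre variances are 0.2100, 0.2484 and 0.2356, mean 0.2313. Pooled variance is 0.46 × 0.54 = 0.2484. So k = 0.2313/0.2484 = 0.931, 1/√k = 1.036 and 1.96 × 1.036 = 2.031. Type I error = 2 × [1 − Φ(2.031)] = 4.2%. Power = Φ(3.605 − 2.031) = Φ(1.574) = 94.2%.

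| Centre rates (equal centres) | k | Interval too wide by | Type I error | Power |
|---|---|---|---|---|
| 46/46/46% | 1.000 | 0% | 5.0% | 95.0% |
| 36/46/56% | 0.973 | 1.4% | 4.7% | 94.7% |
| 30/46/62% | 0.931 | 3.6% | 4.2% | 94.2% |
| 20/46/72% | 0.819 | 10.5% | 3.0% | 92.5% |

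**Simulation check.** 20,000 simulated trials with three centres of 120 women gave type I errors of 4.9% with every centre at 45.8%, 4.6% at 35.8/45.8/55.8% and 3.7% at 25.8/45.8/65.8%. The formula gives 5.0%, 4.7% and 3.8%.

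**Unequal centres.** If recruitment followed the delivery counts (1259, 7501 and 1607, total 10,367), one centre would hold 7501/10,367 = 72% of women. With 30/46/62% assigned to the centres in every possible order, type I error is 4.3% to 4.7%, power is 94.3% to 94.7% and intervals are 1.4% to 3.2% too wide.

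**Numeric outcome.** The same formulas apply to the t test, with k equal to one minus the share of outcome variance explained by centre. A share of 10% gives 3.9% type I error and 93.8% power; a share of 20% gives 2.8% and 92.1%.

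**The case against.** Several objections carry weight.

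- **The error is on the safe side and small.** Ignoring centre cannot create false positives, and it costs nothing if centres are alike. Eligibility is narrow (primiparous women, single term births above 2500 g, no separation into critical units), which should reduce differences in risk mix. The 20/46/72% case assumes a 52-point spread that nothing in the article supports. All of this stands and limits the point to lost precision.
- **Adjusted analyses are planned and could include centre.** True. The tests named for relating allocation to the outcomes are nevertheless the pooled ones, and the article does not say that the main comparison accounts for centre.
- **A covariate and subgroup list may sit in an analysis plan or full protocol not shown.** This also stands. The absence of such a list is not part of the point.

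A reader might go further and infer that covariates and subgroups will be picked after seeing the results. That could matter: in an assumed example with 360 women and five covariates, choosing the most favourable covariate subset rejected a true null 10.0% of the time, and five independent looks at 5% give 1 − 0.95^5 = 22.6%. But the article does not say this. "From the initial analysis, analyses of subgroups and adjusted analyses will be used" can equally mean that crude comparisons come first and adjusted ones follow. In the same assumed example, adjusting for covariates imbalanced at p < 0.20 rejected only 4.2%. Only the ambiguity can be criticised.

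**Conclusion.** The point holds in a modest form. The design stratifies by centre in effect, and the stated comparisons do not follow the design. Over the range taken as plausible (36/46/56% to 30/46/62%, equal centres), the intervals are 1.4% to 3.6% too wide, true type I error is 4.7% to 4.2%, and 0.3 to 0.8 points of power are given away from 95%. These sizes rest on assumed centre rates and centre sizes, since the article gives neither rates nor planned recruitment by centre.

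It would be wrong to conclude that the trial's error bars are invalid or too narrow: they err on the wide side, and only if centres differ. No stated alpha or power figure is shown to be wrong. How duration of exclusive breastfeeding should be modelled over time is a separate question and is not decided here. The adjustment sentence is a secondary matter of unclear wording.

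**What to change.** In the Statistical analysis section, state that the primary comparison and the relative risks account for centre. For example, use a Mantel-Haenszel relative risk stratified by centre for exclusive breastfeeding at 1, 4 and 6 months, and a centre-stratified or centre-adjusted comparison for duration.

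Replace the closing sentence with a statement that adjustment factors and subgroups are fixed before outcome data are seen, and that subgroup analyses are exploratory.

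The cost is wording only. Centre is known for every woman and no new data are needed. The sample size is still to be calculated after the pilot, so it can be set to match the centre-stratified analysis, and the article already provides for documented protocol amendments.
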